#### Exclusion criteria

Patients are excluded if they meet any of the following criteria:

1.CTR is not between 0 and 0.5 or the total nodule size is not between 2 and 3 cm.

2.The lesion cannot be completely surgically removed by segmentectomy.3.Lung malignancies other than lung adenocarcinoma confirmed by cytological or histopathological evaluation.4.Prior lung cancer surgery.5.Non-treatment-naïve patients.

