### Endpoints

The primary endpoint is 5 year disease-free survival (5 year DFS). DFS events are defined as tumour recurrence due to lung cancer or death from any cause. Alive patients without recurrence at the last follow-up are defined as censored.

The secondary endpoints are lung function, 5 year overall survival, the site of tumour recurrence and metastasis, segmentectomy completion rate, radical segmentectomy (R0 resection) completion rate and surgery-related complications.

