### Eligibility criteria

#### Inclusion criteria

All enrolled patients should meet the following criteria:

Written informed consent.18–80 years old (including cut-off value) at the time of signing the informed consent.Eastern Cooperative Oncology Group (ECOG) score of 0 or 1.No prior lung cancer surgery.Invasive LUAD confirmed by intraoperative or postoperative pathological evaluation.A single pulmonary nodule with a predominantly ground-glass component or pure ground-glass on CT, or multiple pulmonary nodules but the main lesion is the above-mentioned nodule.The CTR of the nodule ranges from 0 to 0.5, and the total size is between 2 and 3 cm.No evidence of nodal or distant metastasis.The tumour is evaluated to be completely removed via segmentectomy by thoracic surgeon.No prior radiotherapy or chemotherapy.

Exclusion criteria

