### Treatment

#### Segmentectomy and lymph node dissection

Pulmonary GGOs that are evaluated to be removed via segmentectomy by thoracic surgeons could be included in the study. Anatomical segmentectomy could be single segmentectomy (eg, S3 resection), combined segmentectomy (eg, S7+S8 resection), basal segmentectomy (eg, S7–S10 resection) and trisegmentectomy (eg, left S1–S3 resection). In addition, the use of wedge resection to manage the patient’s other non-major lesions is allowed in this study.

Based on the results of previous studies, there was no lymph node metastasis in lung cancer with a CTR<0.5,^9^ so there is no further provision for mediastinal lymph node dissection in this study, and the surgeon could choose the extent of mediastinal lymph node dissection according to personal experience. The lymph nodes exposed during the operation need to be removed and sent for pathological examination.

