#### Intraoperative frozen pathological evaluation criteria

All primary tumours are sent to the pathology room for frozen section diagnosis immediately after resection. Frozen pathology is taken from the maximum diameter of the tumour. Diagnosis is based on the 2015 WHO classification criteria.^12^ Lesions diagnosed as invasive lung adenocarcinoma/non-small cell lung cancer by intraoperative frozen are included in this study.

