#### Calculation of sample size

According to the results of previous studies, for patients undergoing lobectomy with tumour sizes of 2–3 cm, CTR≤0.5 and the 5 year DFS was 97.0% after surgery.^13^ In this trial, we assumed that the expected 5 year DFS for these patients undergoing segmentectomy is 95%. A sample size of 292 achieves 90.193% power to detect a non-inferiority proportion of 90% (5% as the non-inferior boundary) using a one-sided exact test with a target significance level of 0.0250. Considering a possible dropout rate of 5%, a total of 307 cases need to be included in this trial.

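### Exclusion criterion 2 and the nodal inclusion criterion carry no time point while inclusion is completed only after resection, so the text permits (but does not require) dropping incompletely resected or node-positive patients from the DFS and R0 analyses.

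*Protocol article*

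**What the plan says.** All references are to the protocol article.

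- **Resectability.** Inclusion criteria: "The tumour is evaluated to be completely removed via segmentectomy by thoracic surgeon". Exclusion criteria, item 2: "The lesion cannot be completely surgically removed by segmentectomy". The first is a surgeon's judgement; the second is worded as a fact. Neither is dated.
- **Nodes.** Inclusion criteria: "No evidence of nodal or distant metastasis". The section on preoperative CT evaluation and clinical staging defines cN0 by CT or PET/CT, but the criterion does not use that term.
- **When inclusion is completed.** The inclusion criteria require invasive adenocarcinoma on intraoperative or postoperative pathology. The frozen-section section says "All primary tumours are sent to the pathology room for frozen section diagnosis immediately after resection", and the postoperative pathology section again describes patients as included on the basis of paraffin sections. The surgical section adds "The lymph nodes exposed during the operation need to be removed and sent for pathological examination".
- **Removal.** Withdrawal or termination criteria: an enrolment error, illustrated by a patient who does not meet the enrolment criteria, is a ground for withdrawal, with no time limit.
- **Analysis and endpoints.** The primary set is the FAS, made up of enrolled patients who had segmentectomy. The secondary endpoints include "radical segmentectomy (R0 resection) completion rate and surgery-related complications".

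**The concern.** Each passage is unremarkable alone; the problem arises from their combination. The eligibility lists can be closed only when histology is known. By then the completeness of resection is known or about to be, and results from exposed nodes are on their way. A site that checks the lists at that moment could reasonably conclude that an incompletely resected patient meets exclusion criterion 2, or that a patient with a positive node shows evidence of nodal metastasis. The enrolment-error rule then offers a way to withdraw that patient, and the FAS does not prevent it because it covers only those who count as enrolled.

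Two results would suffer. The trial has no control arm, so removing patients with a worse than average outlook raises observed 5-year DFS with nothing to offset it. And if incomplete resection were treated as ineligibility, the R0 rate among those left would be 100% by construction. The trial would then describe segmentectomies that turned out to be complete and node-negative, rather than segmentectomies chosen before surgery. Six centres must apply these criteria alike, and the wording supports two readings that give different populations.

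**Working it through.** **Inputs from the article (Calculation of sample size).** "expected 5 year DFS for these patients undergoing segmentectomy is 95"%; "non-inferiority proportion of 90% (5% as the non-inferior boundary"); one-sided exact test at 0.025; 292 evaluable patients; stated power 90.193%.

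**Step 1: reproduce the design.** Find the smallest r with P(X ≥ r | n = 292, p = 0.90) ≤ 0.025. This is r = 273, so success allows at most 292 − 273 = 19 events.
- Attained one-sided alpha: P(X ≥ 273 | 292, 0.90) = 0.0242.
- Power: P(X ≥ 273 | 292, 0.95) = 0.9019, which matches the article.
- Events expected at 95% DFS: 292 × 0.05 = 14.6, leaving a slack of 19 − 14.6 = 4.4 events.

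**Step 2: effect of removal.** Let S be the true 5-year DFS of all patients given segmentectomy, f the fraction removed after surgery, and q the 5-year DFS of those removed. DFS among those kept is

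S′ = (S − f·q) / (1 − f).

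Example with S = 0.90, f = 0.02, q = 0.50: S′ = (0.90 − 0.01) / 0.98 = 0.9082.

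**Step 3: false-success probability.** Compute P(X ≥ 273 | 292, S′) with S = 0.90. The article gives neither f nor q. The values below are assumptions: f from 0.5% to 3%, and 20% or 50% of those removed failing by 5 years (q = 0.8 or 0.5).

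| Removed (f) | Failing by 5 years | DFS among those kept | P(success) |
|---|---|---|---|
| none | – | 90.0% | 2.4% |
| 0.5% | 20% | 90.05% | 2.6% |
| 0.5% | 50% | 90.2% | 3.1% |
| 1% | 20% | 90.1% | 2.8% |
| 1% | 50% | 90.4% | 4.0% |
| 2% | 20% | 90.2% | 3.1% |
| 2% | 50% | 90.8% | 6.4% |
| 3% | 20% | 90.3% | 3.6% |
| 3% | 50% | 91.2% | 10.0% |

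Every row uses the same 273-of-292 rule, meaning that 292 patients are still analysed after removals. This keeps the comparison like for like. With fewer patients the exact test has a different cut-off and attained alpha (about 1.8% at n = 286 and 2.1% at n = 283), so results at those sizes should not be set against the 2.4% that belongs to 292.

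**Step 4: R0 rate.** If every incomplete resection were ruled ineligible, all retained patients would be R0 and the rate would be 100% whatever the surgical performance. This needs no assumption about f or q, but it does need the literal reading of exclusion criterion 2.

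**The case against.** A reader might infer that the protocol makes a positive margin or a positive node a ground for exclusion, so that the bias is built in. The document does not say this, and several points tell against it.

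- Other exclusions restate inclusion items in the negative (CTR and size, prior lung cancer surgery, prior treatment). Exclusion criterion 2 plausibly does the same for the surgeon's judgement, which the surgical section repeats as the entry test. Its wording is ordinary resectability language and does not mention margins.
- The only definition of node-negative in the article is the preoperative cN0. The surgical section also relies on earlier results showing no nodal metastasis at CTR below 0.5, so on the protocol's own premise few patients, if any, would leave by that route.
- Pathology is used expressly for inclusion in one respect only, histological type.
- The FAS is described as following intention to treat, and a margin-positive segmentectomy patient who counts as enrolled fits it.
- An R0 completion rate makes sense only if non-R0 patients stay in the denominator, which suggests that a prediction was intended.

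These points stand: the stronger reading fails, and the nodal part is clearly the weaker one. They do not close the gap. Intention has to be inferred, the enrolment-error rule has no time limit, and no sentence keeps R1/R2 or pN+ patients in. Nor is this a detail left to a fuller document, since the article prints both eligibility lists and the fault lies in their wording.

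**Conclusion.** The point holds as an ambiguity with a predictable direction of bias; it is not an exclusion that the protocol mandates. Two undated criteria, inclusion completed after resection and an open-ended enrolment-error rule together permit the removal of incompletely resected or node-positive patients. That reading conflicts with the R0 rate's role as a secondary endpoint.

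The effect on the primary analysis cannot be sized from the document. On the assumed ranges it runs from negligible (false success 2.6% against 2.4%) to material (about 10%), and nothing in the article favours the upper end. The circularity of the R0 rate does not depend on those ranges, only on the literal reading being applied. The design arithmetic itself is sound: 273 of 292, alpha 0.0242, power 0.9019. A correction is worthwhile because it is cheap and protects the primary endpoint of a single-arm trial.

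**What to change.** 1. Word exclusion criterion 2 as the surgeon's preoperative judgement that complete removal by segmentectomy is not possible, to match the inclusion criterion.
2. Word the nodal part of the inclusion criterion as cN0, as defined in the preoperative staging section.
3. State that intraoperative and postoperative pathology settle one eligibility question only: invasive adenocarcinoma, yes or no.
4. State that R1/R2 margins and pN+ found at or after segmentectomy are outcomes, not enrolment errors under the withdrawal section, and that these patients stay in the FAS, the DFS analysis and the R0 denominator.

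The cost is a few sentences. The assessments are already made and the sample size is unchanged. The one downside is that observed DFS and the R0 rate may be slightly less favourable.

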### Withdrawal or termination criteria

All data in this trial are obtained based on existing examinations and procedures and the trial does not cause any additional harm to patients. The specifics of the patient’s withdrawal from this study are as follows:

The patient’s data shall not be used for the clinical study.Patient enrolment error (eg, patient does not meet enrolment criteria).Patients voluntarily propose to withdraw from the trial.

### Treatment

#### Segmentectomy and lymph node dissection

Pulmonary GGOs that are evaluated to be removed via segmentectomy by thoracic surgeons could be included in the study. Anatomical segmentectomy could be single segmentectomy (eg, S3 resection), combined segmentectomy (eg, S7+S8 resection), basal segmentectomy (eg, S7–S10 resection) and trisegmentectomy (eg, left S1–S3 resection). In addition, the use of wedge resection to manage the patient’s other non-major lesions is allowed in this study.

Based on the results of previous studies, there was no lymph node metastasis in lung cancer with a CTR<0.5,^9^ so there is no further provision for mediastinal lymph node dissection in this study, and the surgeon could choose the extent of mediastinal lymph node dissection according to personal experience. The lymph nodes exposed during the operation need to be removed and sent for pathological examination.

### Procedures

#### Preoperative CT imaging evaluation and clinical staging

All patients are required to undergo a thin-slice (1 mm) contrast-enhanced CT scan of the chest before enrolment. According to the CT scan results, the long diameter of the tumour is the maximum diameter of the tumour (solid component+ground-glass component) on the CT cross-section. The size of the solid component is the maximum diameter of the solid component on the CT cross-section. CTR is defined as the ratio of solid component size to tumour diameter. For pure ground-glass nodules in which there are no solid components, the CTR is 0. cN0 is diagnosed when the short axis of lymph nodes of intrapulmonary, interlobar, hilar and mediastinal are shorter than 10 mm on contrast-enhanced CT or no uptake of lymph nodes on PET/CT.^10^ The staging in this study is performed using the 8th edition of the TNM lung cancer staging system.^11^ Patients will be admitted to the hospital for surgery after the CT or PET-CT is evaluated by the radiologist, and the interval is 1 month.

#### Intraoperative frozen pathological evaluation criteria

All primary tumours are sent to the pathology room for frozen section diagnosis immediately after resection. Frozen pathology is taken from the maximum diameter of the tumour. Diagnosis is based on the 2015 WHO classification criteria.^12^ Lesions diagnosed as invasive lung adenocarcinoma/non-small cell lung cancer by intraoperative frozen are included in this study.

#### Postoperative pathological evaluation criteria

The postoperative pathological diagnosis of the tumour using paraffin sections is based on the 2015 version of the WHO classification criteria, and patients with lung adenocarcinoma are included in this study. All pathology reports are evaluated by two experienced pathologists.

### Statistical analysis

#### Analysis sets

Full analysis set (FAS): determined according to the intention-to-treat principle, including all enrolled cases who have undergone segmentectomy.

Per-protocol set (PPS): subset of the FAS population, including all cases that meet the protocol and have completed case report form.

In this trial, FAS analysis is used for baseline data and validity analysis. The main efficacy indicators are will be analysed in the FAS and PPS data sets. However, the analyses of the FAS data set are considered primary. When analyses of the FAS and PPS reach consistent conclusions, confidence in the conclusions can be increased. For the FAS data set, the missing data after the fall are estimated using the last observation carried forward method.

The laboratory examination data and adverse events will be analysed using SPSS and Stata software.

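### The primary analysis set is called intention-to-treat but admits only patients who received segmentectomy, so conversions fall outside both defined sets

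*Protocol article*

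**What the plan says.** Under Analysis sets, the protocol article defines the FAS as "determined according to the intention-to-treat principle, including all enrolled cases who have undergone segmentectomy". The per-protocol set is a "subset of the FAS population, including all cases that meet the protocol and have completed case report form". The section adds that "the analyses of the FAS data set are considered primary". No set of all enrolled patients, or of all patients in whom segmentectomy was planned, is defined.

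Three other places bear on this:

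- Endpoints lists among the secondary endpoints "segmentectomy completion rate, radical segmentectomy (R0 resection) completion rate and surgery-related complications". No denominator is given for either rate.
- Inclusion criteria require that "The tumour is evaluated to be completely removed via segmentectomy by thoracic surgeon", which is a judgement about the planned operation. They also require "Invasive LUAD confirmed by intraoperative or postoperative pathological evaluation", which can be settled only during or after surgery.
- Exclusion criteria remove a patient if "The lesion cannot be completely surgically removed by segmentectomy", with no statement of when this is judged.

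**The concern.** The label and the rule contradict each other. Intention-to-treat keeps a patient according to the treatment planned; this rule keeps a patient according to the treatment received.

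The trial asks whether segmentectomy is a suitable operation to plan for these tumours. A patient whose planned segmentectomy becomes another resection is part of the answer. Under the stated rule that patient contributes to no defined analysis of the primary endpoint, in the main set or in the supporting one. Agreement between the two sets, which the article says would raise confidence, cannot reveal the problem because both carry the same selection.

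With no control arm to share the selection, any difference in outcome between completed and converted patients passes directly into the comparison with 90%.

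**Working it through.** **1. Who is in which set, by the plain wording**

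| Enrolled patient planned for segmentectomy | FAS | PPS |
|---|---|---|
| Segmentectomy done, R0 | yes | yes, if otherwise compliant |
| Segmentectomy done, R1 | yes | possible |
| Another resection done instead | no | no (subset of FAS) |

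A completion-rate endpoint has meaning only if the third row can occur. Computed in either defined set, that rate is n/n = 100%. The R0 rate is not fixed in this way, because an R1 segmentectomy stays in the FAS.

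**2. The plan's own figure**

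Inputs from Calculation of sample size: threshold 0.90, expected DFS 0.95, one-sided exact test at 0.025, n = 292.

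- The smallest r with P(X ≥ r | 292, 0.90) ≤ 0.025 is r = 273, with exact alpha 0.0242.
- Power is P(X ≥ 273 | 292, 0.95) = 0.90193, which matches the stated 90.193%.
- Total: 292 × 1.05 = 306.6, giving 307 as stated.

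The sample-size arithmetic is therefore not at issue.

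**3. Effect on the primary test (assumptions, not document figures)**

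Let c be the share converted and d the 5-year DFS in converted patients. Suppose DFS in all planned patients is exactly 90%, so that success would be a false conclusion. DFS in the FAS is then

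p = (0.90 − c·d)/(1 − c),

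and the chance of false success is P(X ≥ 273 | 292, p). With c = 5%:

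| d | p | False success |
|---|---|---|
| 70% | (0.90 − 0.0350)/0.95 = 91.05% | 8.3% |
| 80% | (0.90 − 0.0400)/0.95 = 90.53% | 4.6% |
| 90% | (0.90 − 0.0450)/0.95 = 90.00% | 2.4% (no bias) |
| 97% | (0.90 − 0.0485)/0.95 = 89.63% | 1.5% |

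The last row borrows the 97.0% that the sample-size section gives for lobectomy. That figure concerns lobectomy in general, not conversion from segmentectomy, so it serves only to show that the sign can reverse.

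**4. Sensitivity to n**

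The exact test is discrete, so these figures move with n. At c = 5% and d = 70%, n = 291 (critical value 273, exact alpha 1.5%) gives 5.5% instead of 8.3%. At c = 2% and d = 80%, p = (0.90 − 0.016)/0.98 = 90.2%, and false success is 3.1% at n = 292 but 2.2% at n = 301. The table in step 3 holds n fixed so that only d varies.

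**5. Effect on sample size**

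If 5% of 307 convert (about 15), the FAS is 307 − 15 = 292 before any loss to follow-up, so the whole 5% dropout allowance is spent. A further 5% loss leaves 277 (292 × 0.95 = 277.4), where power at a DFS of 95% is 84.3%.

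**The case against.** The strongest reply accepts the mislabelling and disputes the consequences. Much of it stands.

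- **Completion rate.** A reader might infer that this endpoint is emptied of information. The article does not support that. It assigns the FAS to baseline data, validity analysis and the main efficacy indicators, and it states no denominator for the completion rates. An all-enrolled denominator is compatible with the text, since the FAS wording itself treats enrolled cases as the wider group. The 100% result is conditional on using the FAS.
- **R0 rate.** A reader might infer that failures of R0 are removed too. Under the FAS wording they are not. They would be lost only if exclusion criterion 2 were judged after the attempt. That reading is possible, because some eligibility is settled after resection, but the matching inclusion criterion is a surgeon's evaluation that points to the planning stage.
- **Direction of bias.** It is tempting to say that dropping conversions overstates DFS. That needs converted patients to do worse, and the documents do not report how they do. Step 3 of the working shows inflation, no effect or the reverse. The Treatment section also cites earlier results of no nodal metastasis at CTR below 0.5, which suggests that node-driven conversions would be rare.
- **Meaning of the rule.** Having undergone segmentectomy could be stretched to include an attempted one. The text does not say so.

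None of this removes the contradiction. Nor is it a detail left to an analysis plan: the article states the primary set and its rule outright, so a plan that follows it inherits the problem and a plan that departs from it contradicts the article.

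**Conclusion.** The FAS definition is wrong as written. It claims intention-to-treat and applies an as-treated rule. Since the per-protocol set is nested in it, patients converted to another resection are in no defined set and drop out of the primary 5-year DFS analysis. This conclusion rests on the article's wording alone and needs no assumption.

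The numerical effect does need assumptions. At n = 292, 5% conversions and DFS of 90% in all planned patients, false success lies between 1.5% and 8.3% as DFS in converted patients goes from 97% down to 70%, against an exact level of 2.4%. These are illustrations, not bounds: conversion rate and outcome are both absent from the documents, and the figures shift with n. A claim that the trial's DFS will be overstated, or that its completion and R0 rates are uninformative, goes beyond what the documents support.

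**What to change.** Under Analysis sets:

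1. Define the FAS as all enrolled, pathologically eligible patients taken to theatre for planned segmentectomy, whatever resection is completed.
2. Use this set for the primary DFS analysis, and name it as the denominator of the segmentectomy completion rate and the R0 rate.
3. Make receipt of segmentectomy a condition of the per-protocol set.

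Under Exclusion criteria, word criterion 2 as a pre-operative assessment, in line with the inclusion criterion on the surgeon's evaluation, so that it cannot remove failed or incomplete segmentectomies afterwards.

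The cost is a text amendment and keeping converted patients in follow-up. It should be made well before the estimated primary completion in December 2028, while those patients can still be followed. The DFS estimate may be slightly less favourable. If the 95% in the sample-size section is meant for completed segmentectomies only, then with 5% conversions at a DFS of 80% (assumed) the all-planned rate is 0.95 × 95% + 0.05 × 80% = 94.25%, and power at n = 292 is about 76%. At 90% in converted patients it is 94.75% and about 86%. The sponsor should therefore say which population the 95% describes.

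### Last observation carried forward is prescribed for the primary analysis set without exempting DFS; applied to 5-year DFS it conflicts with the censoring rule and biases the single-arm test towards success

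*Protocol article*

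**What the plan says.** Four statements in the protocol article bear on how a patient lost to follow-up enters the primary result.

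- **Endpoints.** "The primary endpoint is 5 year disease-free survival (5 year DFS"), with recurrence or death from any cause as the event. For patients without an event: "Alive patients without recurrence at the last follow-up are defined as censored".
- **Analysis sets, population.** The FAS is defined as "including all enrolled cases who have undergone segmentectomy", so it keeps patients who are lost later. The main efficacy measures are analysed in the FAS and the per-protocol set (PPS), but "the analyses of the FAS data set are considered primary".
- **Analysis sets, missing data.** "For the FAS data set, the missing data after the fall are estimated using the last observation carried forward method". The wording appears to mean data missing after dropout. It follows directly on the rules for the main efficacy measures and is not limited to any endpoint.
- **Calculation of sample size.** "A sample size of 292 achieves 90.193% power to detect a non-inferiority proportion of 90% (5% as the non-inferior boundary"), by a one-sided exact test at 0.025. The 292 are raised to 307 for 5% dropout.

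The article names no time-to-event estimator and does not say how a censored patient enters the exact test.

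**The concern.** Consider a patient last seen disease-free at 2 years. Under the Endpoints section, the status after 2 years is unknown. Under LOCF, the 2-year status is copied to 5 years and the patient becomes a success. Both rules cannot govern the same patient for the same endpoint. The exact test needs a yes or no for everyone, and LOCF is the only stated rule that supplies one.

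The direction of the error is fixed: a patient lost before a recorded event can only be carried forward as event-free. The trial has no control arm in which the same error could offset it, because the comparison is with a fixed 90%. The decision also rests on few events, at most 20 among 307 patients, so a small number of unseen events matters.

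**Working it through.** **Inputs from the protocol article.** Null 5-year DFS 0.90; expected 0.95; exact one-sided test at 0.025; 292 evaluable; 307 enrolled; 5% dropout. **Assumed here:** exponential DFS, loss unrelated to prognosis, and loss either uniform over 5 years or all just after surgery.

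**1. Reproduce the plan's figure.** With N = 292 the smallest passing count is 273 disease-free (19 events):
- P(X ≥ 273 | 292, 0.90) = 0.0242
- P(X ≥ 273 | 292, 0.95) = 0.90193, which matches the stated 90.193%.

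**2. Same test on all 307 FAS patients, no loss.** The smallest passing count is 287 (20 events): type I error 0.0214, power 0.907.

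**3. What LOCF does to the hurdle.** Suppose 307 − 292 = 15 patients are lost at once and scored as successes. The remaining 292 then need only 287 − 15 = 272 disease-free, where the plan's own test on 292 needs 273. P(X ≥ 272 | 292, 0.90) = 0.0396, against 0.0242 for 273.

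**4. General form.** With loss proportion d, true DFS p, and e the chance that a lost patient's event is recorded before loss:

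apparent DFS = 1 − [(1 − d)(1 − p) + d·e]

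For very early loss e = 0. For uniform loss e = 1 − (1 − p)/(−ln p); at p = 0.90 this is 1 − 0.1/0.10536 = 0.0509.

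At d = 0.05 and p = 0.90:
- uniform: 1 − (0.095 + 0.0025) = 0.9025; P(X ≥ 287 | 307, 0.9025) = 0.030
- early: 1 − 0.095 = 0.905; P(X ≥ 287 | 307, 0.905) = 0.041

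| Loss | Type I error, uniform | Type I error, early |
|---|---|---|
| 0% | 0.021 | 0.021 |
| 5% (protocol) | 0.030 | 0.041 |
| 10% (assumed) | 0.040 | 0.073 |
| 20% (assumed) | 0.071 | 0.199 |

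At true DFS 0.95 and 5% loss, apparent power rises from 0.907 to 0.924 (uniform) or 0.938 (early).

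**5. Kaplan-Meier with the protocol's censoring.** Simulated with 307 patients and 5% uniform loss (runs of 10,000 and 30,000):
- mean estimate at true DFS 0.90: 0.900, so no bias
- type I error with a log-log lower bound: 0.017 and 0.019
- power at 0.95 with that bound: 0.884 and 0.879
- type I error with a plain (untransformed Greenwood) bound, 10,000 runs: 0.046

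The last line matters for the fix: with so few events, a plain bound would be further above 0.025 than LOCF is.

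**The case against.** **LOCF may not be meant for DFS.** The sentence does not name DFS. LOCF is a repeated-measures device, and lung function is a secondary endpoint. The Endpoints section gives a rule specific to DFS, and a specific rule can be read as overriding a general one. This has force: one cannot say that the trial will count lost patients as successes. What stands is that the sentence is unrestricted, sits directly after the rules for the main efficacy measures in the primary set, and is nowhere reconciled with censoring.

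**A reader might infer a far larger error.** Three stronger readings are not supported.

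- *Hidden events among dropouts.* If 30% or 50% of lost patients have unseen events and all loss is just after surgery, LOCF gives false success of about 12% or 30%. Neither rate has a source in the protocol, and immediate loss is the worst case. Kaplan-Meier is also inflated: 6.8% and 18.9% in simulation for early loss. With uniform loss the pairs are 5.4% (LOCF) against 3.5% (Kaplan-Meier), and 7.6% against 5.1%. Much of that error comes from informative loss and not from LOCF.
- *Patients not yet at 5 years.* Carrying status forward for everyone short of 5 years in December 2028 would give an error of about one half under uniform accrual. But the sentence appears to concern dropout, not patients still being followed. That figure measures the accrual timetable, which is a separate matter.
- *The PPS offers no check.* If the PPS drops lost patients, it does not score them as successes, so the comparison of FAS with PPS could show a discrepancy. It cannot reveal hidden events, but neither can Kaplan-Meier.

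**The SAP may settle it.** An estimator left to the SAP would be no finding. Here the protocol itself states a method for its primary set that clashes with its own endpoint definition.

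**Conclusion.** The missing-data rule is wrong as written, because it reaches the primary endpoint and contradicts the censoring rule there. If it is applied to 5-year DFS, the bias is always towards success. At the plan's 5% loss the breach is modest: type I error of 0.030 to 0.041 against 0.025, and an estimate too high by 0.25 to 0.5 points. It grows with more loss. The sizes rest on the assumed loss patterns and on non-informative loss; the direction does not. Informative loss would enlarge the error, but it would also bias Kaplan-Meier and so needs its own sensitivity analysis. The text does not establish that LOCF is intended for DFS, only that nothing excludes it.

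**What to change.** 1. State that LOCF does not apply to DFS or OS. If it is meant for lung function or other repeated measures, say so.
2. Estimate 5-year DFS in the FAS by Kaplan-Meier, censoring as the Endpoints section already says. Declare success if the lower one-sided 97.5% confidence bound exceeds 90%. Name a log-log bound, since the plain one does not hold 0.025 here.
3. Add a sensitivity analysis that counts patients lost before 5 years as events, to address informative loss. Report it as an extreme bound and not as a second hurdle: at true DFS 95% and 5% loss its expected value is 0.95 × 0.95 = 90.25%, and it would clear the 287-of-307 rule only about 3% of the time.

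Cost: a few sentences of analysis wording and no new data. Power at true DFS 95% becomes about 0.88 with 307 enrolled and 5% loss, against the stated 0.90.
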